**PRODUCT:**

Number of investigational products: 1

Proposed ICD code: 571.8

proposed indication**:** TREATMENT OF PATIENTS IN ETA 'PEDIATRIC AFFECTED BY NONALCOHOLIC STEATOHEPATITIS.

**PRODUCTS DATA OF EXPERIMENT:**

- Dietary product for special medical purposes: Krilling D®
- Pharmaceutical product: dietary product
- Active ingredient: docosahexaenoic acid + Vitamin D3
- Dosage: 225 mg DHA + 800 IU of Vitamin D
- MAH: Italchimici
- Producer Company: Italchimici
- Pharmaceutical Form: pearls
- Route of administration: Oral
- maximum treatment duration for experimentation: 24 weeks (6 months)
- Any association with drugs with the same indication: No
- Concomitant drug therapies with drugs with other indications? NO
- Comparison type:
- Other medications: NO
- Placebo: YES
- The same drug to clinical assays: NO

**Other (please specify):** All patients will be prescribed a balanced low-calorie diet (25-30 cal / kg / d; carbohydrates 50-60%; 23-30% fat, 15-20% protein, fatty acids: saturated 2/3 and 1/3 unsaturated; ω6 / ω3 ratio = 4: 1).

In addition to all patients it will be recommended an activity 'physical program of 30 minutes a day, at least 3 times a week.

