**INTRODUCTION TO TRIAL**

The non-alcoholic fatty liver disease (NAFLD) Paediatric has in recent years reached epidemic proportions. currently NAFLD affects 3-10% of normal-weight children and 70-80% of those who are overweight / obese. Over the next 10-20 years, many countries WILL doubling the frequency of the disease, making it emergency identify effective therapeutic strategies. the NASH is characterized by hepatomegaly and / or elevated aminotransferase levels and hepatic steatosis in the absence of other known causes of liver disease and / or consumption of alcohol. Histologically is characterized by inflammation and necrosis of the liver tissue. The main risk factor for the development of NASH is obesity. The pathogenesis is still not well known, several studies suggest that oxidative stress is implicated in the pathophysiology of NASH.

The recruited patients receive two capsules a day containing) docosahexaenoic acid (DHA); ii) Vitamin D3, or placebo for 24 weeks. there is provided a follow-up laboratory-instrumental at baseline (screening visit) and every 6 months up to 12 months (52 weeks).

From a clinical point of view the expected result, eliminated hepatocyte oxidative stress caused by inflammation and fibrosis, will be to interrupt the evolution of the disease to cirrhosis and organ failure.

The therapeutic options currently available for the treatment of pediatric patients with NASH are represented by diet and the increase daily physical activity.

The drugs that will be used in this study have the following characteristics:

- DHA is an essential polyunsaturated fatty acid that belongs to the very long chain Omega 3 series, of which the fish fats, derived from alpha-linoleic precursor are rich. As a precursor of eicosanoids, DHA has an anti-inflammatory enzyme effect, which modulate the metabolism of lipoproteins. For these characteristics it has been suggested activity in the prevention of metabolic syndrome.

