**AIM OF THE RESEARCH**

The evidence available thus provide the rationale for the use of DHA and Vitamin D in children suffering from non-alcoholic steatohepatitis, the aim of reducing the oxidative stress in load of hepatocytes and slow the progression of the fibrotic process to load of the liver parenchyma. It is therefore proposed to recruit patients aged between 4 and 16 years, with non-alcoholic steatohepatitis (NASH, documented histologically), with good liver function, to a randomized double-blind study providing for the administration of a mixture containing DHA and vitamin D vs. a placebo for a period of about 6 months (24 weeks).

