**CRITERIA FOR THE INTERRUPTION OF TREATMENT:**

Adverse events

All adverse events which occurred during the course of the clinical study will be reported in the case report form that will be completed for each individual patient. An adverse event is defined as any adverse change with respect to the patient's pre-treatment basal conditions regardless of whether the event is or is not considered treatment-related. This includes all relevant laboratory abnormalities and new illnesses that occur or worsen during the treatment period. It is considered treating any medication administered during the study. The intensity of adverse events will be evaluated using a 3-point scale (mild, moderate, severe). It must also be always documented the relationship between the adverse event and the treatment in progress.

| Severity of adverse events | |
| --- | --- |
|  | |
| Mild | You notice a malaise, but do not have any impairment of normal daily activities |
| Moderate | Malaise enough to reduce or affect normal daily activities |
| Severe | Incapacitating with inability to work or perform normal daily activities |
| Life-threatening | It represents an immediate threat to the patient's life |

Any adverse reactions will also be classified according to the "grading" NCI / NIH (see Annex). In case of serious adverse events, the Ethics Committee will be warned.

Laboratory tests on the safety of the treatment:

- The toxicity data be evaluated based on the exams required by the study design.

The treatment will be suspended the following conditions:

- Toxicity of grade III-IV according to the NCI / NIH criteria;

- If the patient expressing the intention to stop treatment

The expected period of the Experiment: 12 months in total including six months for enrollment and 24 weeks in patient enrolled.

SCHEDULED DATE FOR START OF EXPERIMENTS: October 2013

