**TYPE OF STUDY AND EXPERIMENTAL DESIGN AND ITS DESCRIPTION:**

Study: prospective, randomized, Phase III, placebo, with double blindness.

The patients will be randomized into two groups to receive oral emulsion of docosahexaenoic acid (DHA) + Vitamin D3 for oral use pearls (the experimental group), or placebo (control group) that will be made of an inert substance ( corn oil) of that aspect of the pearls of DHA and vitamin D, and will be provided with the product KRILLING D from Italchimici. The requirements concerning the arrangements for daily administration and conservation of the drug will be provided by the Unit of Hepatometabolic Diseases of our Hospital to parents at enrolment.

The assessment of candidates to the inclusion in the protocol in question will be carried out by the Medical of Unit of Hepatometabolic Diseases.

The formulation of the suitability will be based on clinical assessment and the instrumental and laboratory investigations performed. At enrolment in the protocol, we will ask the parents to sign the attached consent form informed the study.

The expected duration of treatment is 24 weeks (approximately 6 months). All patients (and those randomized to the pearl of DHA and vitamin D, both those in the control arm) will be followed every 6 months at our Hepatometabolic Diseases and will undergo check-up, serological and instrumental exams. At the time of study and each semester it will be collected a blood sample for serum bank.

If any patient’s toxicity will not be logged continue the treatment until the end of the period. In case of onset of toxicity or some serious adverse event in some patients, the study will be immediately suspended. Should patients experience an increase in transaminases (equal to or> 6 x N), will be subjected to a clinical and laboratory control with monthly dosing of liver function tests (GOT, GPT, total and fractionated bilirubin, alkaline phosphatase, gamma GT, proteinaemia total, albumin, Quick time and immunoelectrophoresis protein).

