**METHOD FOR MANAGEMENT, EVALUATION AND PROCESSING AND DISTRIBUTION OF PRELIMINARY AND FINAL DATA:**

At the screening visit (T0), the following controls are provided:

- Complete medical history;

- Complete physical examination;

- Blood count with differential;

- Liver function parameters: AST, ALT, total and fractionated bilirubin, alkaline phosphatase, gamma GT, albumin, total protein and electrophoresis proteinaemia, INR, total cholesterol, triglycerides, blood glucose, alpha-fetoprotein, LDH;

- Renal function parameters: blood urea nitrogen and creatinine;

- Electrolyte balance: Sodium, potassium, calcium and magnesium;

- serum iron and ferritin

- OGTT;

- Vitamin D

- Ultrasound abdomen.

The T1 visit, carried out after 6 months of treatment, will be performed the following investigations:

- Clinical evaluation;

- blood exam completed;

- Liver function parameters: AST, ALT, total and fractionated bilirubin, ALP, gamma GT, albumin, total protein and electrophoresis proteinaemia, INR, total cholesterol, triglycerides, blood glucose, alpha-fetoprotein, LDH;

- Vitamin D values

- 5 ml of blood for serum bank.

At the end of study, performed after 12 months of study, we will be performed the following investigations:

- Clinical evaluation;

- blood exam completed;

- Liver function parameters: AST, ALT, total and fractionated bilirubin, alkaline phosphatase, gamma GT, albumin, total protein and electrophoresis proteinaemia, INR, total cholesterol, triglycerides, blood glucose, alpha-fetoprotein, LDH;

- Vitamin D values

- 5 ml of blood for serum bank

-Liver biopsy.

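### The background diet of 25-30 cal/kg/day applies to every child from age 4 with no minimum daily intake; at assumed weights of 20-30 kg it amounts to 500-900 kcal/day

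*Protocol*

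**What the plan says.** The diet is set in the Protocol under PRODUCTS DATA OF EXPERIMENT, in the entry for other specifications: "All patients will be prescribed a balanced low-calorie diet (25-30 cal / kg / d". A split into carbohydrate, fat and protein follows. The section gives no lower bound on total intake, no adjustment for age, and no indication whether actual or ideal weight is the multiplier.

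Under AIM OF THE RESEARCH the plan is to "recruit patients aged between 4 and 16 years", and POPULATION STUDY repeats that age range. The inclusion and exclusion criteria contain no weight or BMI limit; entry rests on biopsy, ultrasound and laboratory findings. The introduction says "The main risk factor for the development of NASH is obesity", and it also puts the prevalence of NAFLD in normal-weight children at 3-10%.

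On follow-up, patients "will be followed every 6 months at our Hepatometabolic Diseases", and the schedule describes "The T1 visit, carried out after 6 months of treatment" as the next visit after screening. Treatment lasts 24 weeks; no separate duration is given for the diet.

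**The concern.** A rate per kilogram with no floor scales down in proportion to weight. The same rule governs a 4-year-old and a 16-year-old, and it is a low-calorie prescription at both ends. For a heavy adolescent the result is moderate. For a light young child, followed literally, it may be very little food for about six months in a growth period.

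What is at stake is the safety of a small subgroup of minors. The diet is common to both arms, so the treatment comparison is not at risk.

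**Working it through.** **Inputs from the protocol.** Rate: 25-30 cal/kg/day for all patients, with cal read as kcal. Age: 4-16 years. Minimum intake: none. Weight or BMI criterion: none.

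**Inputs assumed.** Body weights, because the protocol states none. A minimum of 1000 kcal/day, used only to show how a floor would act, with 800 and 1200 as alternatives.

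The protocol states no total daily intake, so there is no figure of its own to reproduce.

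**Step 1: daily intake = rate × weight.** The last column shows the effect of the illustrative floor.

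| Assumed weight (kg) | 25 × kg | 30 × kg | With a floor of 1000 kcal/day |
|---|---|---|---|
| 20 | 500 | 600 | at least 1000; whole range replaced |
| 25 | 625 | 750 | at least 1000; whole range replaced |
| 30 | 750 | 900 | at least 1000; whole range replaced |
| 35 | 875 | 1050 | 1000-1050; lower part removed |
| 40 | 1000 | 1200 | unchanged |
| 50 | 1250 | 1500 | unchanged |
| 60 | 1500 | 1800 | unchanged |

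**Step 2: where a floor F would act.** Even the top of the range misses F below F/30 kg. The bottom of the range meets F from F/25 kg.

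- F = 800: 800/30 = 26.7 kg; 800/25 = 32 kg.
- F = 1000: 1000/30 = 33.3 kg; 1000/25 = 40 kg.
- F = 1200: 1200/30 = 40 kg; 1200/25 = 48 kg.

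So with F = 1000 there are three zones: below 33.3 kg the floor replaces the whole range, between 33.3 and 40 kg it removes the lower part, and from 40 kg it has no effect.

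**Step 3: what would catch a problem.** The adverse-event section is broad: "An adverse event is defined as any adverse change with respect to" the pre-treatment condition. The design section adds: "In case of onset of toxicity or some serious adverse event in some patients, the study will be immediately suspended". Both act only once something has gone wrong. The first routine visit after baseline falls at month 6, about when the 24 weeks of treatment end. The one monthly control in the protocol is triggered by a rise in transaminases, not by intake or growth.

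**The case against.** The strongest reply is that no harm is shown. The protocol gives neither body weights nor a paediatric energy requirement, so calling 500-900 kcal/day too low is clinical judgement. That is correct, and the size of any deficit against need cannot be derived from the document. The distance to 1000 kcal/day is not such a deficit, since 1000 is only an example, and moving it from 800 to 1200 moves the weight below which the whole range is replaced from 26.7 to 40 kg.

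Exposure is also conjectural. Entry needs a biopsy and ultrasound compatible with the disease, obesity is named as the main risk factor, and only 66 children are planned at one centre. The 3-10% figure is a prevalence among normal-weight children; it shows that light children are not excluded by the disease, not that they will be biopsied and enrolled. The number affected may be zero.

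Finally, a specialist unit assesses suitability, the rate is itself a range, and families may withdraw. These make literal delivery of such an intake less likely. They do not supply a floor: the top of the range still gives only 600 kcal/day at 20 kg, and adverse-event reporting and withdrawal come after the event. Nothing in the text tells the clinician when to depart from the rate.

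A reader might infer that the trial will underfeed its young participants, or that their safety goes unmonitored. The document supports neither. It has broad adverse-event recording and a suspension rule, and it says nothing about how many small children will enter.

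**Conclusion.** The point holds as a limited safety matter of wording. The rule as written covers all patients from age 4 without a minimum, and at assumed weights of 20-30 kg it prescribes 500-900 kcal/day. This rests on reading cal as kcal, on the assumed weights, and on clinical judgement that such an intake is low for a growing child. No problem is claimed at 50-60 kg.

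A reader might also infer an effect on the trial's result. There is none to claim: the diet is the same in both arms, so it introduces no between-arm bias, and it does not enter the power calculation. The change is worth considering because it concerns minors and costs almost nothing; it is not a flaw in the design.

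**What to change.** Keep the rate and add one clause to the diet entry under PRODUCTS DATA OF EXPERIMENT, identical in both arms:

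*25-30 kcal/kg/day, but not below an age-appropriate minimum daily intake set by the unit's clinicians, with energy set individually where the per-kg rate falls below it.*

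The clinicians should choose the minimum. The 1000 kcal/day used above is not a recommendation: it equals 1000/20 = 50 kcal/kg at 20 kg and 1000/25 = 40 kcal/kg at 25 kg, so whether it suits the smallest children needs their judgement. The macronutrient percentages stay as they are.

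The cost is one clause. Eligibility, visits, endpoints and analysis do not change. The small downside is a slightly less uniform background diet in the lightest children, by the same rule in both arms.

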**EVALUATION OF THE TREATMENT:**

The primary efficacy parameter is the normalization of transaminases and reduced liver fibrosis, documented by liver biopsy.

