**Research objectives**

Efficacy and tolerability of treatment with DHA and vitamin D in children with nonalcoholic steatohepatitis:

- Evaluating the effectiveness of DHA + Vitamin D in improving 'NAFLD Activity Score' (NAS) of the disease

- Evaluation of the tolerability of the administration of DHA and vitamin D

- Evaluating the effectiveness of DHA and vitamin D in improving haematochemical values 'marker' of the evolution of the metabolic syndrome

**Primary endpoint:** the reduction of the score of the disease in the experimental group compared to the control group.

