**DATA ANALYSIS AND EVALUATION OF RESULTS:**

Sample Size and Statistical Analysis

Statistical tests: Fisher's exact test

Type I error (Alpha) 0.05

Probability (Pi): 0.10 vs 12:45

sample size (n): 33 per arm

Power = 83.00%

***

Consider that 10% of the placebo group reduces the NAS to values ​​<2 (1.2) and that with 30 patients per group will have an 83% power to declare statistically significant at a 0.05 alpha level an absolute difference 35% of the response (45% experimental group - 10% of the placebo group).

Whereas a 10% drop-out, the number of final patients to be enrolled will be equal to 66.

Randomization

Randomization is achieved by the use of random number tables, the sequence is generated by the computer with allocation in a sealed envelope (epidemiology and statistics service). The key to encode the patient will be taken from the pharmacy, as the doctor in charge will remain blinded to the allocation of the patients in the two arms, one with mixture of DHA and vitamin D, and the placebo.

The analysis will be "intention to treat", understood each patient in the original randomization arm.

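### The protocol labels two different outcomes as primary, and its 83% power applies only to a NAS response, not to transaminase normalisation with reduced fibrosis

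*Protocol*

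**What the plan says.** Three sections of the protocol bear on the primary comparison.

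- **Research objectives.** The entry labelled as primary endpoint is "the reduction of the score of the disease in the experimental group compared to the control group". The first objective above it identifies the score: "Evaluating the effectiveness of DHA + Vitamin D in improving 'NAFLD Activity Score' (NAS) of the disease". No cut-off, scale or time point is attached.
- **Evaluation of the treatment.** The whole section is one sentence: "The primary efficacy parameter is the normalization of transaminases and reduced liver fibrosis, documented by liver biopsy". NAS is not mentioned. The sentence does not say whether a child must meet both parts, whether each part is tested separately, or whether either is enough.
- **Data analysis and evaluation of results.** The sample size assumes that "10% of the placebo group reduces the NAS to values" below 2, with an unexplained 1.2 in brackets after the cut-off. The difference to be detected is "45% experimental group - 10% of the placebo group". The test is Fisher's exact test at alpha 0.05, with 83% power at 30 per arm and 66 children enrolled after a 10% allowance for drop-out. This section does not use the word primary.

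No section ranks these outcomes.

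**The concern.** Two sections each declare a primary outcome, and the two do not measure the same thing. As far as the NAFLD Activity Score is used in this protocol, it is a disease score read against a cut-off. The other outcome combines a blood test with fibrosis on biopsy. A treatment could succeed on one and fail on the other, and the protocol does not say which result would decide the trial.

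The sample size supports only the NAS response. If the transaminase and fibrosis outcome governs, the trial has no stated power.

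That outcome is also a poor primary for this population. The inclusion criteria set an upper limit on ALT (below 10 times the upper limit of normal) but no lower limit, and require a biopsy consistent with NAFLD/NASH but no minimum fibrosis stage. A child who enters with normal transaminases cannot normalise, and one without fibrosis cannot improve. Such children would dilute the difference between arms.

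**Working it through.** **1. The stated power.** Inputs from Data analysis and evaluation of results: response rates 0.10 and 0.45, n = 30 per arm, "Statistical tests: Fisher's exact test", "Type I error (Alpha) 0.05". Sidedness is not stated; two-sided is assumed.

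Power = Σᵢ Σⱼ b(i; 30, 0.10) · b(j; 30, 0.45) · 1[Fisher p(i, j) ≤ 0.05], where b is the binomial probability and the sum runs over all outcomes.

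- Two-sided, 30 per arm: **0.830**, which matches the stated 83%.
- One-sided, 30 per arm: 0.898, which does not match, so the protocol's figure is the two-sided one.
- Two-sided, 33 per arm: 0.864.
- Enrolment: 60 × 1.10 = 66, as stated.

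The calculation is sound for a binary NAS response with these rates.

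**2. The same sample size applied to the other labelled primary.** The protocol gives no rates for normalised transaminases with reduced fibrosis, so the rates below are assumptions that show the range. Two-sided Fisher, 30 per arm:

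| Assumed control | Assumed experimental | Power |
|---|---|---|
| 5% | 20% | 24% |
| 10% | 30% | 37% |
| 20% | 45% | 44% |
| 30% | 65% | 71% |
| 20% | 55% | 74% |

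The last two rows keep the protocol's 35-point difference and still fall short of 83%, because power also depends on the control rate.

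**3. Dilution.** If a fraction f of children in each arm cannot meet the outcome because of their entry values, and all are counted, a difference D among the others becomes (1 − f) × D overall. The protocol gives no information on f.

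**4. Type I error if either outcome could be declared primary.** For two independent tests of size s, the chance of at least one false positive is 1 − (1 − s)².

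- If each test had size exactly 0.05: 1 − 0.95² = 0.0975.
- The only named test is conservative. By exact enumeration, two-sided Fisher at 30 per arm has size 0.0094 when both arms respond at 10%, and at most 0.0274 at any common rate.
- Two such tests at the maximum: 1 − (1 − 0.0274)² = **0.054**. At a common 10% rate: 1 − (1 − 0.0094)² = 0.019.
- At 33 per arm the maximum size is 0.0356, giving 1 − (1 − 0.0356)² = 0.070.

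Positive correlation between the outcomes would lower these figures. Another test, with size closer to 5%, would raise them.

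**The case against.** The best defence is that the protocol is nearly coherent. The objective, the labelled primary endpoint and the sample size all concern NAS, and the only test named suits a binary outcome. On that reading the sentence under Evaluation of the treatment is a loosely worded outlier, and a statistical analysis plan that is not shown may already settle the matter. The first part is fair and points to the natural repair. It does not remove the contradiction, because that sentence plainly calls something else primary.

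Four stronger readings are tempting, and the document does not support them.

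- **That there are three primary endpoints.** Only two outcomes carry the label. The NAS response can be read as the working form of the labelled score reduction, which mentions no mean change. An error rate of 14.3% (1 − 0.95³) falls with that count.
- **That the type I error nearly doubles to 9.75%.** That needs two independent tests of exact 5% size. Fisher's exact test at this sample size is well below that.
- **That the primary result can be chosen once the data are seen.** The protocol does not fix the endpoint, but an analysis plan could do so before unblinding. Only the first half can be shown here.
- **That the transaminase and fibrosis outcome cannot be scored in every child.** Children with normal transaminases or no fibrosis at entry can be counted as non-responders. The result is dilution.

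One further counterpoint stands: the inclusion criteria set no minimum NAS either, so a child could enter near the response cut-off. The NAS response is preferable because it is the outcome the sample size supports, although it shares this weakness.

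**Conclusion.** The point holds as a contradiction between two sections, and it must be reconciled. Research objectives and Evaluation of the treatment name different primary outcomes, and no rule ranks them. The 83% power is correct for a NAS response of 10% against 45% with 30 evaluable children per arm, and for that outcome only. For transaminases and fibrosis the power is unknown; the 24% to 74% range rests on assumed rates and shows only that 83% cannot be taken over.

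The effect on type I error is secondary. It is bounded at about 5.4% for two independent two-sided Fisher tests at 30 per arm (about 7% at 33), and depends on the tests used and their correlation. The weight of the point lies in the undecided hypothesis and the missing power.

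**What to change.** - Name one primary endpoint in identical words under Research objectives, Evaluation of the treatment, and Data analysis and evaluation of results. The choice is the sponsor's, but the binary NAS response is the only candidate that the sample size supports.
- State its cut-off unambiguously. As printed, below 2 followed by 1.2 in brackets could mean strictly below 2, or could be a misprint for the values 1 and 2. Say also how a child already at or below the cut-off at entry is counted.
- Tie it to the 12-month biopsy, the only follow-up biopsy in the visit schedule.
- Make normalisation of transaminases secondary, analysed in children with raised values at entry and stating whether AST, ALT or both are meant. Make fibrosis a separate secondary outcome.
- If the sponsor keeps transaminases and fibrosis as primary, say whether it is a composite or co-primary, withdraw the 83%, and recalculate power from rates for that outcome.

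With the NAS response as primary, the cost is a wording amendment: 66 children and the planned visits stand, and the 83% stands provided that the 10% and 45% were meant for the cut-off finally stated. Keeping transaminases and fibrosis as primary could change the sample size.
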